**Inclusion criteria:**

- Expecting mother with a fetal diagnosis of intrauterine growth restriction (IUGR) defined by estimated birth weight ≤ 10th percentile for gestational age and gender based on the Alexander growth curves.
- ≥ 6 weeks from expected due date.

**Exclusion Criteria:**

- Multiple congenital abnormalities (other than CHD)
- Known fetal chromosomal disorder
- Maternal illicit drug or alcohol intake

**Study plan:**

Dating will be by ultrasound or reliable clinical dating by ACOG standards (33). A dedicated study coordinator will evaluate volunteers to enroll from pregnant patients at the Washington University Medical Center (WUMC) in St. Louis, MO. The Institutional Review Boards of WUMC will approve this study before initiation. A total of eighty consenting women will be randomized to one of two arms POM juice vs POM juice placebo in a 1:1 ratio. The Women’s Health Center at WUMC includes a State-approved collaborative practice of Washington University attending physicians, nurse practitioners, and residents that serve all patients regardless of payer status. The WUMC Center for Advanced Medicine offers a second site for recruitment where university affiliated private practices are located. We anticipate 1-2 patients enrolled per week.

***Treatment group****:* Expecting mothers in this group will be randomized to start a daily regimen of 8 oz glass of pomegranate juice (POM Wonderful). They will keep a daily diary documenting their compliance. They will continue this daily intake up until delivery of their infant.

***Placebo group:***These women will start a daily regimen of an 8 oz of pomegranate free juice placebo that matches taste, calories, and appearance to regular pomegranate juice but lacks polyphenols that contains the same substances without polyphenols. They will also keep a diary of daily intake to help ensure compliance similar to the treatment group. They too will continue to take the placebos up until the time they deliver.

***Both groups:*** All women will be followed up (called) on a weekly basis to assess compliance. Upon delivery, cord blood will be collected and sent for ellagic acid, a polyphenic component. All placental material will be sent for formal pathological exam in addition to the specialized studies outlined below.

Placental Evaluation:

**Overview**: We will test the hypothesis that the active agents in pomegranate extract modulate the villous structure of the placenta, reduces the effects of exogenous stimuli, or both, in the human placenta of women diagnosed to have intrauterine growth restriction.

***Patient population:*** Placentas will be collected after delivery from all pregnancies randomized to the four study groups described above. Systematic random sampling (34, 35) of placentas midway between the chorionic and basal plate and excluding the placental edge, in area 5 B from our published work (36) will yield five specimens for formalin fixation, random orientation in paraffin blocks, and microscopic analyses below. Five separate specimens will be frozen in liquid nitrogen and prepared in Tri-Reagent for protein, RNA and DNA analysis. This number of samples controls for random variation in the placental tissue.

**Analyses to be conducted:** We will evaluate the structure, cellular composition, and expression of selected markers of oxidative stress in the placentas collected from the pregnancies of this study. W*e* have extensive experience in all aspects of the collection, morphometry, micrography, immuno- histochemistry, enzyme immunoassays, RNA and protein analyses of placental tissues.

1: Gross structure of the placenta.We will obtain the placental weight, width (short axis), breadth (long axis), thickness (average of three equidistant measurements perpendicular to the cross section of the chorionic and basal plates of the placenta), and volume of the placenta by water displacement. We also will photograph the chorionic plate to validate the cord insertion site and vascular pattern on the chorionic surface, as this is related to placental function.

2: Morphometry of villous tree:We will quantifythethree types of villi (stem, intermediate, and terminal). A morphometric grid intersects tissue and cell structures to offer volume density expressed as cm3, while the lines that intersect tissue offer assessments of surface density, expressed as m2. Each placenta provides five embedded samples that are arranged in a tissue array on a single slide. Twenty digital images at 200 X final magnification are obtained from random fields and grids with a spacing of 40µm are overlain on each image for analysis. NIH Image J software (<http://rsbweb.nih.gov/ij/>) and point and line intersects mentioned above are recorded and volumes and surface areas, respectively, of placental items of interest. The morphometry analysis will quantify the relative contributions of the three villous sub-types allows us to test the hypothesis that pomegranate enhances the number of terminal villi (i.e. exchange related villi), compared to control, and that POM juice and POM extract are equal in their effects on the villous development.

3: Assessment of cellular components within villi. We will assess each villus for the relative contributions of trophoblasts by cytokeratin 7 staining, fetal blood vessels (endothelial lectin expression), connective tissue (collagen staining; macrophage immunostaining), and fibrin as a second series of evaluations to test our above hypothesis of less collagen and increased vasulature.

4: Assessment of trophoblast biology**.** *Proliferation index* in cytotrophoblasts will be evaluated by immunohistochemical staining for Ki67 antigen, which is a marker for cells that are progressing through the cell cycle. *Apoptosis* will be assessed by immunoblot analyses and immunohistochemical staining for the cl-Cyt18 and cl-Parp, as cytoplasmic and nuclear markers of apoptosis, respectively. An apoptotic index for syncytiotrophoblast and cytotrophoblasts will be calculated by dividing the fraction of positive staining cytotrophoblast by the total number of cells, or positive areas in syncytiotrophoblast normalized to surface density of this component from the morphometry evaluation. We additionally quantify the levels of cl-Cyt18 and cl-Parp by immunoblot analysis of extracts from previously frozen placental villi, with actin as a loading control. *Differentiation* will be assayed using IHC to detect hCG and hPL, both specifically produced by trophoblasts. The immunofluorescence stained expression of these hormones in syncytiotrophoblast will be quantified using confocal microscopy of tandem sections to the ones used for morphometry, as an assessment of trophoblast differentiation. Villous tissues will be evaluated by RT-PCR analysis of mRNA and western immunoblot analysis for both hCG and hPL again normalized using actin as a loading control..

5: Assessment of oxidative stress in villous tissues. We will quantify the markers of exogenous stress by immunoassay, immunohistochemistry, or western immunoblot. Each of the chosen dependent variables for this analysis assesses different components of ROS generation. *Heat shock protein 90* will be assessed by immunohistochemistry and western immunoblot analysis.

*Lipid hydroperoxide* assay will evaluate **l**ipid peroxidation in placental extracts using an assay kit (Calbiochem) with results expressed as μM/mg protein. *Nitrotyrosine assay* and immunohistochemistry for nitrotyrosine residues takes advantage of the fact that 3-nitrotyrosine, which is produced following the reaction of superoxide with nitric oxide, forms peroxynitrite which modifies tyrosine residues on proteins will be determined by commercial chemi-luminesence assay (Millipore) as μg/mg protein. *Paraoxonase 1 expression* is regulated by polyphenols in hepatocytes and this enzyme activates PPAR-, a key transcription factor for placental development. We will determine expression by immunoblot activity using an antibody from Sigma and the aryl esterase activity of the enzyme using phenyl acetate as substrate, reported as one unit equals 1 μmol of phenyl acetate hydrolyzed/ min. *Superoxide dismutases (SOD)* as key antioxidant enzymes will be measured by commercial assay (Caymann Chemical) that detects all three types of SOD activity (Cu-ZnSOD, MnSOD, & FeSOD). SOD activity is expressed as U/mg protein.

6: Microarray assessments of villous tissues exposed to POM juice, POM extract, or placebos. We will prepare RNA for gene microarray analyses as we have done previously (Roh et al. Placenta). We will test the hypothesis that pomegranate juice, extract or both, modulate the gene expression profile to enhance the cassette of genes involved in tissue repair, cytotrophoblast proliferation, limits expression of genes involved in apoptosis while enhancing genes involved in autophagy. This profile predicts prosurvival (e.g. increased autophagy), less cellular injury (i.e. apoptosis), and overall tissue repair (re-epithelialization of villous injury).

**Interpretation of results:** We expect pomegranate-exposed placentas to show less evidence of oxidative stress, more trophoblast mass, and less evidence of fibrin deposition microscopically and by immunoblotting. We expect less apoptosis and more evidence of trophoblast differentiation in the pomegranate group. We will consider any differences in the light of biological significance, also, as small statistically significant differences may prove relevant to the infant outcomes. Although highly unlikely based on the known effects of pomegranate, we will note any adverse effect from pomegranate extract, such as enhanced oxidative stress, increased fibrin deposition as a sign of injury, or diminished terminal villi lower than control.

Infant Neurobehavior: All infants will have a formal Dubowitz neurologic exam and an attention evaluation using the Hammersmith Neonatal Neurological Examination Optimality score at term equivalent (38-41 weeks post menstrual age). Furthermore, formal neurodevelopmental follow up will take place at 18-24 months of age.

MRI Evaluation

If clinically stable, MRI will be undertaken without sedation at term equivalent (38-41 weeks CGA). The MRI evaluation will include the following analysis:

a) Systematic qualitative scoring of the nature and extent of brain injury

b) Diffusion analysis of the cortical, white matter and posterior limb of the internal capsule to generate apparent diffusion coefficients (ADC).

c) Spectroscopy over the left basal ganglia

d) Brain metrics measuring the length of certain regions of the brain and comparing to standardized values

e) Assessment of MRI developmental indices such as volume and surface folding (SBM)

| **Measure** | **White Matter** | **Gray Matter** |
| --- | --- | --- |
| Qualitative | WM lesion score/  ventriculomegaly | Cortical and DNGM injury score |
| Metrics | Frontal lobe volume, | Intrahemispheric volume loss, ventricular size |
| Volumetry | Total myelinated and unmyelinated WM volumes | Total cortical gray matter, DNGM and CSF volumes  Hippocampal volume |
| Diffusion | Two measures (ADC, RA) each measured on 8 pairs of volume –derived lesions | Two measures (ADC, RA) on:   1. 6 pairs of surface-based regions 2. 8 pairs of volume-derived regions |
| MRS | N/A | Lactate and NAA measures over the L basal ganglia |
| SBM | NA | Four measures (cortical surface area, average sulcal depth, integrating folding index, and percentage buried cortex) |

Figure 6: Surface based renderings of prematurely born infants (five infants left side) and one term born infant (right) demonstrating marked differences in the surface brain development.

[figure not shown]

[figure not shown]

Perinatal data will also be collected. Items will include:

- Birth weight
- Gestation
- Apgars, resuscitation needed in DR and cord gas characteristics
- Any markers of neonatal illness related to admission to an intensive or special care unit such as encephalopathy, need for intravenous or parenteral nutrition or any related morbidities of preterm birth, e.g. intraventricular hemorrhage.

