**Outcome measures:**

1. **Placenta**

a) Morphometry – weight and size of the placenta.

b) Micrography - number of terminal villi, vasculature and collagen content.

c) Immuno- histochemistry – proliferation, apoptosis and differentiation.

d) Enzyme immunoassays - Heat shock protein 90, Lipid hydroperoxide, Nitrotyrosine assay Paraoxonase 1 expression and Superoxide dismutases

e) RNA and protein analyses of placental tissues - RNA for gene microarray analyses

1. **Pregnancy Outcomes**
   1. Complications of pregnancy – extent of pre-eclampsia, preterm labor
   2. Gestation at delivery
   3. Need for resuscitation at delivery
   4. Cord gas characteristics at delivery
2. **Brain injury and development at term by MR Imaging (see table 2) based on:**
   1. Qualitative MRI injury- white matter injury (WMI) and gray matter injury (GMI)
   2. Brain Metrics on MR imaging
   3. Diffusion- apparent diffusion coefficient (ADC) and fractional anisotropy (FA)
   4. Spectroscopy- lactate and NAA levels in the basal ganglia
   5. Advanced MRI development indices – brain volumes, surface based morphology (SBM, folding indices)
3. **Neurobehavior at term equivalent and neurodevelopmental outcome at 18-24 months** MDI and PDI by Bayley Scale of Infant Development (BSID III) (> 2SD from the norm, score ≤ 70)

***Table 1.*** Summary of the study and procedures for infants recruited into the study

| **Age** |  | **Pregnancy** | **Birth** | **38-41 weeks CGA** | **Discharge** | **18-24 months** |
| --- | --- | --- | --- | --- | --- | --- |
| Maternal data |  | X | X |  |  |  |
| Clinical data |  |  | X | X | X | X |
| Ellagic acid |  |  | X |  |  |  |
| MRI imaging |  |  |  | X |  |  |
| Neurodevelopmental  Behavioral measures | Neurologic/  Sensory |  |  | Dubowitz | Hearing |  |
|  | Attention |  |  | HNNE  attention |  |  |
|  | Global cognition |  |  |  |  | BSID-III  Cognitive |
|  | Motor |  |  |  |  | BSID-III  Motor, Neuro |
|  | Language |  |  |  |  | BSID-III  Language |

* HNNE- Hammersmith Neonatal Neurological Examination Optimality Score

* MRS- MR Spectroscopy; SBM- Surface-based morphology

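### Relative shares of villous types are named as the test of the number of terminal villi, but no count is described and the tested quantity is unclear

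*Protocol*

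**What the plan says.** All references are to the protocol.

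- **Hypothesis and its test.** Placental Evaluation, item 2 (Morphometry of villous tree), says the morphometry will "quantify the relative contributions of the three villous sub-types allows us to test the hypothesis that pomegranate enhances the number of terminal villi".
- **Outcome.** Outcome measures, Placenta, item b, reads "Micrography - number of terminal villi, vasculature and collagen content".
- **Measurement.** Item 2 describes the grid twice: "A morphometric grid intersects tissue and cell structures to offer volume density expressed as cm3", and "the lines that intersect tissue offer assessments of surface density, expressed as m2". It then says that "point and line intersects mentioned above are recorded and volumes and surface areas, respectively, of placental items of interest".
- **Whole-organ volume.** Item 1 (Gross structure) includes the "volume of the placenta by water displacement".
- **Sampling.** The Patient population paragraph takes the specimens from one designated area (5 B), at mid-depth and away from the edge.
- **Adverse direction.** Interpretation of results treats fewer terminal villi than control as a harmful sign, without saying whether number, amount or share is meant.
- **Test.** Biostatistical Analyses gives a t-test or Mann-Whitney test for continuous variables in general and names no villous variable.

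**The concern.** Three different quantities are in play: how many terminal villi there are, how much terminal villous tissue there is, and what share of the villous tree is terminal. The hypothesis and the outcome list name the first. The sentence that names the test uses the third. The recorded grid counts lead to the second.

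The units do not settle which is meant. A volume density is a fraction and has no unit, and a surface density is an area per unit volume. The protocol gives them in cm3 and m2, which are units of totals. Either the word density is loose or the units are wrong.

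At stake is the reading of the villous result. A share need not follow an amount when total villous tissue or placental size differs between arms. Such a difference is possible here: weight and size of the placenta are themselves outcomes, and the pregnancies are growth-restricted. The protocol presents placental mechanism as a gap that this study is to fill, so the tested quantity should be clear before analysis.

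**Working it through.** The protocol states no villous figure, effect size or power for this outcome, so there is nothing to reproduce. The check is whether the quantities named can diverge. All baseline amounts below are assumptions.

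**1. Share against amount.** Let T be the amount of terminal villi and O the amount of stem plus intermediate villi.

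Share = T / (T + O). If T is multiplied by a and O by b, the new share is p·a / (p·a + (1 − p)·b), where p is the baseline share. It rises only if a > b, whatever happens to T itself.

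Assumed control: stem 60, intermediate 60, terminal 80 cm3, so the share is 80/200 = 40.0%.

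| Scenario | Terminal amount | Share |
| --- | --- | --- |
| A: all types +20% | 96 cm3 (+20%) | 96/240 = 40.0% (unchanged) |
| B: terminal +10%, others +30% | 88 cm3 (+10%) | 88/244 = 36.1% (falls) |
| C: terminal −10%, others −30% | 72 cm3 (−10%) | 72/156 = 46.2% (rises) |

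**2. Range over the assumed baseline share.**

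| Baseline share | Scenario B | Scenario C |
| --- | --- | --- |
| 30% | 26.6% | 35.5% |
| 40% | 36.1% | 46.2% |
| 50% | 45.8% | 56.25% |
| 60% | 55.9% | 65.9% |

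The direction does not depend on the baseline chosen.

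**3. Can the planned data give the amount?** Yes. Total terminal volume = volume fraction × placental volume. Put the 80 cm3 in an assumed placenta of 400 cm3: the fraction is 80/400 = 0.20. A placenta of 480 cm3 with the same fraction has 0.20 × 480 = 96 cm3, so the +20% of scenario A is recovered. The fraction here is per unit of placenta. The share among villous types (0.40 in this example) is a different ratio and cannot be multiplied by placental volume in its place. Total surface area follows in the same way, as surface density × placental volume.

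**4. Can they give the number?** No. Number = total terminal volume / mean volume per villus, and the protocol describes no measurement of the second term. At the same total volume, a mean villus volume ×0.8 gives 1/0.8 = 1.25 times the number, and ×1.25 gives 0.8 times the number.

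**The case against.** The strongest reply is that the protocol does not confine itself to shares. Item 2 says that the three villous types will be quantified and that volumes and surface areas come from the grid, and item 1 supplies the whole-organ volume. The cm3 and m2 can be read as intended totals. A reader might infer that the plan measures only shares and so cannot address the amount of terminal villi, or that its result will point the wrong way. The documents support neither inference. Totals are obtainable, and a flat or opposite result arises only if the share is what is tested. Nothing in the protocol suggests that scenario C is likely.

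Three further points have weight:

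- A larger placenta with unchanged composition would show in the separate weight and size outcome, so it would not go unseen.
- The composition of the villous tree is a legitimate target, because the placental overview hypothesis concerns villous structure.
- Exact derivation of a laboratory variable is often left to a statistical analysis plan, which is not at hand.

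What remains is a mismatch that the protocol itself states. It fixes a hypothesis about number, an outcome about number, and a test by relative contributions, and these do not agree. No sentence says that densities will be multiplied by placental volume. That the right inputs are collected makes the repair cheap, but it does not show that the plan uses them.

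**Conclusion.** The point holds as a mismatch between hypothesis, outcome and named measure. The protocol says number, describes no count, names relative contributions as the test, and pairs density with units of totals. If the share is the tested variable, it can stay at 40.0% while the amount rises 20%, or move against the amount in either direction (36.1% with +10%, 46.2% with −10%). Those figures rest on assumed baseline amounts and growth factors. Only the direction is general, and it held for assumed baseline shares from 30% to 60%.

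It would go too far to say that the planned data cannot answer a question about terminal villi. They can answer one about total volume and surface area, though not one about number.

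The consequence is limited. This is a mechanistic placental outcome in a pilot whose primary outcomes are brain injury or delayed development, and no sample-size figure depends on it. The correction is desirable but not critical.

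**What to change.** In item 2 of Placental Evaluation and in item b of the placental outcomes:

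1. Name the variables compared between arms: total terminal-villus volume per placenta (volume fraction × placental volume by water displacement, cm3) and total terminal-villus surface area per placenta (surface density × placental volume, m2). State that the fraction is taken over the whole placental reference space, not over villous tissue alone.
2. Report the terminal share beside these totals as a measure of villous composition.
3. Correct the units of density: none for a volume fraction, and area per unit volume for a surface density.
4. Replace number of terminal villi with these quantities in both places, and make no claim about number. Say in Interpretation of results that a reduction in terminal villi refers to the same totals.

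**Cost.** The change needs wording and one multiplication per placenta for each total, on data already planned. The totals carry the measurement error of the placental volume. They also assume that density in the sampled area (5 B, edge excluded) represents the whole placenta, so they extrapolate to tissue that was not sampled. The protocol should state this assumption. It is also a reason to keep the share in the report.

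### The cytotrophoblast apoptotic index is mis-stated: as written, it varies with cell count or cell mix as well as with apoptosis

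*Protocol*

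**What the plan says.** Under Placental Evaluation, item 4 (Assessment of trophoblast biology), apoptosis is assessed by staining for cl-Cyt18 and cl-Parp. For cytotrophoblasts, the index is formed by "dividing the fraction of positive staining cytotrophoblast by the total number of cells". For syncytiotrophoblast, the same sentence uses "positive areas in syncytiotrophoblast normalized to surface density of this component from the morphometry evaluation". The two markers are also measured by immunoblot with actin as loading control.

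No other part of the protocol restates or corrects the cytotrophoblast formula. Apoptosis is listed under Outcome measures, item 1c. The Biostatistical Analyses section names brain injury or delayed development as the primary outcomes and treats the placental measures as exploratory work on mechanism.

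The protocol also states what it expects to find:

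- Interpretation of results: "We expect pomegranate-exposed placentas to show less evidence of oxidative stress, more trophoblast mass", and "We expect less apoptosis and more evidence of trophoblast differentiation in the pomegranate group".
- Item 3: "less collagen and increased vasulature".
- Item 6: pomegranate will "enhance the cassette of genes involved in tissue repair, cytotrophoblast proliferation".

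**The concern.** An apoptotic index should answer one question: what share of the cytotrophoblasts is apoptotic? The written formula does not do so on either natural reading.

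- **Literal reading.** The numerator is a fraction and is divided again by a number of cells. The result is not a proportion, and it shrinks as more cells are counted.
- **Charitable reading.** If the word for the numerator is a slip for a number, positive cytotrophoblasts are divided by a total whose cell type is not named. If that total covers all villous cells, the index mixes the apoptotic share with the share of cells that are cytotrophoblasts.

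This matters because the protocol expects pomegranate to change the tissue itself: trophoblast mass, vessels, collagen and proliferation genes. If the arms differ in cell number or composition, the index can differ between them with identical apoptosis, or hide a real difference. The placental measures are there to explain a mechanism, so such a shift could be misread as biology.

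**Working it through.** The protocol gives a formula and no numerical result, so there is no figure to reproduce. The check is algebra with assumed inputs.

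**Notation.** n+ = positive cytotrophoblasts, N = cytotrophoblasts counted, M = all cells counted, f = n+/N = true apoptotic fraction, p = N/M = cytotrophoblast share of all cells. The protocol gives no value for any of these. I take p from 20% to 50%, and f = 5% where a value is needed; the ratios do not depend on f.

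**1. Literal reading, same count in both divisions.** Index = f/N = n+/N². If N is higher by a share s and f is unchanged, the index is multiplied by 1/(1+s):

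- s = 10%: 1/1.10 = 0.909, a fall of 9%
- s = 20%: 1/1.20 = 0.833, a fall of 17%
- s = 50%: 1/1.50 = 0.667, a fall of 33%

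For example, f = 5% with N = 500 gives 0.05/500 = 1.00 × 10⁻⁴, and with N = 600 it gives 0.05/600 = 8.33 × 10⁻⁵. The index can also mask a rise: at s = 20%, f going from 5% to 6% leaves it unchanged, because 0.06/600 = 0.05/500.

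**2. Literal reading, second division by all cells.** Index = f/M. If only cytotrophoblasts rise by 20%, M is multiplied by 1 + 0.2p:

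- p = 20%: 1/1.04 = 0.962, a fall of 4%
- p = 50%: 1/1.10 = 0.909, a fall of 9%

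**3. Numerator read as a number, denominator all cells.** Index = n+/M = f × p.

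- Only cytotrophoblasts rise by 20%: 1.20/1.04 = 1.154 (p = 20%) or 1.20/1.10 = 1.091 (p = 50%), a **rise** of 15% or 9%.
- Only the other cells rise by 20%: 1/(1 + 0.2 × 0.8) = 1/1.16 = 0.862 (p = 20%) or 1/(1 + 0.2 × 0.5) = 1/1.10 = 0.909 (p = 50%), a **fall** of 14% or 9%.
- All cell types rise by 20%: 1.20/1.20 = 1, no change.

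**4. Cytotrophoblasts over cytotrophoblasts.** Index = n+/N = f. The ratio at unchanged apoptosis is 1.000 for any N, M or p.

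The same tissue can therefore give an index that falls, rises or stays put, depending on how one sentence is read. Only the definition in step 4 isolates apoptosis.

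**The case against.** **It is a slip.** The numerator may simply mean the positive-staining portion, so that the laboratory computes an ordinary labelling index. That is the likelier reading, and n+/N² needs both an inner denominator that the text does not state and the assumption that it equals the outer one. This stands, and it is why the literal result cannot be presented as what will happen. It does not rescue the sentence, because the denominator remains unnamed and step 3 applies if it means all cells.

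**The cell count may not vary.** If a fixed number of cytotrophoblasts is counted per placenta and used as the denominator, the artefact vanishes on every reading. The protocol neither states nor rules this out: "Twenty digital images at 200 X final magnification are obtained from random fields" is specified for the morphometry and not for the apoptosis stain. This too stands.

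**A reader might infer a built-in bias towards pomegranate.** The protocol expects more trophoblast mass and less apoptosis, and on the literal reading more cells would look like less apoptosis. The documents do not support going that far. Mass is not a cell count, since more syncytiotrophoblast would add mass without adding cytotrophoblasts. The expected changes are hypotheses, and less collagen is expected alongside more vessels. On the likelier reading, more cytotrophoblasts alone would raise the index, against the hypothesis.

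**Nor can a false-positive rate be attached to the plan.** Take the literal reading with 20% more cells, 40 placentas per arm (80 women at 1:1, all placentas available) and a two-sided 5% test on the log scale. The chance of a significant difference without any true one is about Φ(ln 1.2/(SD × √(2/40)) − 1.96). That is 78% at an assumed log-scale SD of 0.3 and 17% at 0.8. The spread reflects the assumed inputs and is not a property of the protocol.

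**Conclusion.** The point holds as an error of definition. Taken literally, the cytotrophoblast index divides twice and falls by 9% to 33% for 10% to 50% more cells. Taken charitably, with all cells as the denominator, it moves by roughly 9% to 15% in either direction when one cell compartment grows by 20%, assuming cytotrophoblasts are 20% to 50% of cells. No direction of bias can be claimed, and none arises if the laboratory already divides by cytotrophoblasts only.

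The reach is limited. The syncytiotrophoblast index and the actin-normalised immunoblots do not use this formula. Apoptosis is a listed placental outcome but not a primary one, and the trial is a pilot. Severity is minor to moderate. It is worth correcting because the formula is stated and would give a wrong result if followed; it is not a detail left for later.

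**What to change.** Replace the sentence in item 4 with a definition along these lines: the cytotrophoblast apoptotic index is the number of cl-Cyt18 positive (or, separately, cl-Parp positive) cytotrophoblasts divided by the total number of cytotrophoblasts counted in the same fields. Report the syncytiotrophoblast index, positive area normalised to surface density, as a separate measure.

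The cost is one sentence of protocol text, plus a consistent way of identifying cytotrophoblasts in the counted fields. The stain planned in item 3 for the "relative contributions of trophoblasts by cytokeratin 7 staining" may help. However, the protocol does not say that it separates cytotrophoblasts from syncytiotrophoblast or that it is applied to the fields used for apoptosis, so the laboratory needs to confirm how the denominator will be counted.
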